#### Analysis of secondary outcomes

These analyses will be carried out by the trial statisticians. The planned approach for data analysis of secondary outcomes is outlined in Additional file 3. Multivariable analysis will be used to adjust for the following potential confounding variables measured at baseline: age, sex, socioeconomic status, substance use and symptom severity.

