### Outcomes

The trial outcomes are summarised in Table 2.

**Table 2 Tab2:** Summary of outcomes measures for the Task Sharing for the Care of Severe Mental Disorders in a Low-income Country (TaSCS) trial

	Outcome	Measure	Timing
Primary outcome			
1	SMD symptom severity	BPRS-E	Baseline, 12* and 18 months
Secondary outcomes			
1.	Functional impairment^±^	WHODAS 2.0 (12-item)	Baseline, 12 and 18 months
		Local functioning scale	Baseline, 12 and 18 months
2.	Relapse of mental disorder	LCS	Baseline, 12 and 18 months
3.	Service use costs	CSRI	Baseline, 12 and 18 months
4.	Satisfaction with mental health care	Mental health service satisfaction scale (MHSSS)	Baseline, 12 and 18 months
		Qualitative in-depth interviews	From 6 months post-randomisation
5.	Nutritional status	Body Mass Index	Baseline, 12 and 18 months
6.	Service use for physical health conditions	CSRI	Baseline, 12 and 18 months
7.	Medication side effects	ASC	Baseline, 12 and 18 months
8	Patient engagement and adherence	Medication Adherence Measure Clinic attendance	Baseline, 12 and 18 months
9.	Perceived stigma	ISMI	Baseline, 12 and 18 months
10.	Restraint^±^	Proportion chained, restrained or confined in last month	Baseline, 12 and 18 months
11.	Quality of care	Document review	Monthly for 3 months, 6, 12 and 18 months
13.	Adverse events (AEs)	LCS and project reporting mechanisms for AEs	Continuous for serious AEs 6-monthly for other AEs
Mediating variable			
1.	Therapeutic alliance	HAQ	Baseline, 12 and 18 months
Caregiver outcomes			
1.	Perceived stigma	FIS	Baseline, 12 and 18 months
2.	Caregiver burden	FIS	Baseline, 12 and 18 months
3.	Time burden of caring and opportunity costs	CSRI	Baseline, 12 and 18 months
Potential confounding variables			
1.	Sociodemographic characteristics	Structured self-report of age, sex and marital status	Baseline
2.	Socio-economic status	Structured self-report of educational level, occupational status, food insecurity and family size	Baseline
3.	Alcohol use disorder	FAST	Baseline
4.	Khat use disorder	CIDI substance use module	Baseline
5.	Medical co-morbidity or physical disability	Structured self-report	Baseline

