### Sample size calculation

The following formula was used to calculate the required sample size (n):$$ n={2}^{*}{\left[\sigma /\Delta \right]}^2\;{\left({Z}_{\alpha }+{Z}_{\beta}\right)}^2, $$

where delta = non-inferiority margin (mean BPRS-E scores of six points), sigma is the standard deviation of the BPRS-E score (estimated standard deviation of 15 [57]), Z_alpha_ is the standardised mean difference for the probability of type 1 error (alpha = 0.05) and Z_beta_ is the standardised mean difference for the probability of type 2 error (beta =0.1 (that is, power of 0.9). Therefore, a sample size of 107 persons per arm of the trial (that is, a total of 214) is required [58]. No published studies from Ethiopia are available to guide us in our estimation of the intra-cluster correlation (ICC) for study subjects receiving treatment from a specific health centre. We therefore estimate the ICC to be 0.01, which is the median ICC from a review of 31 cluster-based interventions in PHC [59]. Given that there are 13 health centres within the three districts covered by the Ethiopia TaSCS trial, the design effect will be 1 + (n-1)*ICC (where n = number of subjects per cluster). Therefore, the design effect = 1 + (17–1)*0.01 = 1.16. Assuming a worst-case scenario of 30 % loss to follow-up, the required sample size = 214 * 1.30 * 1.16 = 323 participants. For equal numbers in each arm of the trial, the total sample size will be 324 (n = 162 in each arm).

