#### Data analysis approach

Data analysis will follow a detailed statistical analysis plan that specifies all planned analyses. Data analysis will take place using Stata Version 13 (Stata Corporation, College Station, Texas, USA) under the direction of the trial statisticians. All analyses will be masked to study arm until the analysis is finalized and approved by all investigators. Descriptive analyses will include frequency distributions and measures of central tendency and dispersion, as appropriate, with 95 % confidence intervals. Bivariable comparisons will employ χ^2^, Fisher’s exact, Student’s t- or rank-sum tests, as appropriate. All statistical tests will be one-sided at α = 0.05, as we are testing a hypothesis of non-inferiority and not superiority or equivalence.

Analysis will be by intention-to-treat, that is, on the basis of the group to which the participant is allocated randomly at the beginning of the trial. Intention-to-treat has the potential to lead to false acceptance of the hypothesis of non-inferiority in the presence of a true difference if there is a large cross-over from the primary care to the psychiatric nurse service [60]. Therefore, the intention-to-treat analysis will be presented together with the percentage of participants who deviate from the protocol in the following ways: (1) cross-over protocol deviation which is indicated by the percentage who attend for more than two consecutive visits at the service they were not randomised to receive, unless they were referred to that service, and (2) disengagement from care protocol deviation, which is the percentage who miss more than 50 % of their scheduled health facility appointments (not attending within 2 weeks of the appointment date). Per protocol analyses will also be conducted, and the findings presented as a sensitivity analysis. Account will be taken of clustering at the level of the health facility.

Analysis will be carried out on the complete data set at 12 and 18 months. For the primary outcome time-point of 12 months, it would not be appropriate to carry forward the last observation to replace missing data as this would have taken place at the baseline of the study and could, therefore, increase the chance of non-inferiority even in the presence of a difference between the allocated services.

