#### Analysis of primary outcome

The analysis for the primary outcome will be carried out by AHRI in order to ensure masking of the treatment group. The primary outcome measure (change in BPRS-E score) will be analysed using linear regression adjusting for baseline symptom severity. Statistical tests will be one-sided, reflecting our interest in testing the hypothesis that task-shared care is non-inferior. The validity of regression assumptions will be checked using residual plots. For the purpose of safety monitoring, the Phase 1 primary outcome at 12 months will be analysed as an interim analysis. For the purpose of hypothesis-testing for the main trial, Phase 1 and Phase 2 primary outcomes at 12 months will be combined. Both crude and adjusted (for baseline symptom severity, age and sex) effect sizes will be presented for the primary analysis. Exploratory analysis of the non-inferiority of the new intervention in the Phase 1 and Phase 2 participants will be carried out separately.

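### The printed covariate list for secondary outcomes leaves out each outcome's own baseline value, although most are measured at baseline

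*Protocol article*

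**What the plan says.** The section Analysis of secondary outcomes names the adjustment variables as "potential confounding variables measured at baseline: age, sex, socioeconomic status, substance use and symptom severity". The sentence before it points elsewhere for the method: "The planned approach for data analysis of secondary outcomes is outlined in Additional file 3". Data analysis approach adds: "Data analysis will follow a detailed statistical analysis plan that specifies all planned analyses". Neither of those two documents is shown.

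Table 2 schedules functioning, relapse, service use and costs, satisfaction, body mass index, side effects, adherence, stigma, restraint and the caregiver measures at baseline and again at 12 and 18 months. Two secondary outcomes have no baseline: quality of care ("Monthly for 3 months, 6, 12 and 18 months") and adverse events ("Continuous for serious AEs 6-monthly for other AEs").

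The primary outcome is treated differently. BPRS-E is scheduled at "Baseline, 12* and 18 months", and its change score "will be analysed using linear regression adjusting for baseline symptom severity", which is its own baseline.

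**The concern.** The symptom severity term in the secondary list is the own-baseline covariate of the primary outcome. In a model for body mass index or stigma it is the baseline of a different measure. The best single predictor of a continuous follow-up score is usually the same score at baseline, and the printed list does not name it.

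The article justifies its broad set of secondary outcomes by the need to look for harm in a non-inferiority trial. Wider intervals on those outcomes leave harm less well resolved. The Potential confounders section gives chance imbalance as the reason for adjusting at all. Imbalance in the outcome's own baseline is normally the kind that moves its estimate most, and randomisation is stratified only by health centre catchment area.

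**Working it through.** **1. The plan's own figure.** The only sample size is for the primary outcome: margin 6, SD 15, one-sided alpha 0.05, power 0.90.

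- n per arm = 2 × (15/6)² × (1.645 + 1.282)² = 107.05, stated as 107.
- 214 × 1.30 × 1.16 = 322.7, stated as 323 and rounded up to 324 (162 per arm).

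This reproduces. It does not test the present point, but it supplies the scale. With 162 per arm, 30% loss and design effect 1.16, the effective number is 162 × 0.70 / 1.16 = 97.8 per arm.

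**2. The right comparator.** The printed list already includes symptom severity, so the relevant quantity is the gain beyond severity. Take correlations a (follow-up outcome with baseline severity), b (follow-up outcome with its own baseline) and c (the two baselines with each other). Then:

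- R² with both = (a² + b² − 2abc) / (1 − c²)
- variance factor = (1 − R²) / (1 − a²)
- reduction in standard error = 1 − √(variance factor)

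All correlations are assumptions.

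| a | b | c | R² | Variance factor | SE reduction |
|---|---|---|---|---|---|
| 0.3 | 0.3 | 0.5 | 0.120 | 0.967 | 1.7% |
| 0.4 | 0.4 | 0.6 | 0.200 | 0.952 | 2.4% |
| 0.2 | 0.3 | 0.3 | 0.103 | 0.934 | 3.4% |
| 0.3 | 0.5 | 0.5 | 0.253 | 0.821 | 9.4% |
| 0.3 | 0.5 | 0.3 | 0.275 | 0.797 | 10.7% |
| 0.2 | 0.6 | 0.3 | 0.360 | 0.666 | 18.4% |
| 0.3 | 0.7 | 0.4 | 0.490 | 0.560 | 25.2% |

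Worked example, last row: R² = (0.09 + 0.49 − 0.168) / 0.84 = 0.490; variance factor = 0.510 / 0.91 = 0.560; √0.560 = 0.748.

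**3. On the interval scale.** With no covariate, the half-width of a two-sided 95% interval for a standardised difference is 1.96 × √(2/97.8) = 0.280 SD. Adjusting for severity with a = 0.3 gives 0.280 × √0.91 = 0.267. Adding the own baseline gives 0.280 × √(1 − R²):

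- 0.263 for 0.3/0.3/0.5
- 0.242 for 0.3/0.5/0.5
- 0.200 for 0.3/0.7/0.4

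The percentage reductions are the same at any confidence level.

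**4. Chance imbalance.** At randomisation the standard error of a standardised baseline difference is √(2/162) = 0.111, so an imbalance of 1.96 standard errors is 0.218 SD. If that is the imbalance in the part of the own baseline not shared with severity, the severity-adjusted estimate shifts by 0.218 × √(R² − a²). For the same three scenarios:

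- 0.218 × √0.030 = 0.04 SD
- 0.218 × √0.163 = 0.09 SD
- 0.218 × √0.400 = 0.14 SD

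This is the precision loss of step 2 seen from another side, not an additional one.

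**The case against.** **The model may be complete elsewhere.** The article defers the secondary analyses to Additional file 3 and to a statistical analysis plan. The list is headed as potential confounders and does not say that nothing else enters the model. The own-baseline adjustment of the primary outcome, and the Economic analysis section's reference to changes in service costs, suggest that the authors know the value of baseline data. This stands. A reader might infer that the trial will throw this precision away, and the documents do not establish that. What remains is that the article prints a specific list and the list lacks the term.

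**The gain is easily overstated.** A reader might apply 1 − ρ² directly. For ρ from 0.4 to 0.7 that gives a variance reduction of 16% to 49%, or 19% to 96% more participants. That compares with a model holding no baseline covariate, which is not the printed plan. The step 2 figures set aside age, sex, socioeconomic status and substance use, which are also in the list and could take up some of the gain.

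**It does not apply to every outcome.** Quality of care and adverse events have no baseline, and adverse events are the most direct measure of harm. Restraint and relapse are binary or event-type outcomes, for which the linear variance formula does not hold directly. This stands.

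**Nothing is biased.** Randomisation protects the comparison, and the confidence interval already allows for chance imbalance. In a one-sided non-inferiority test a wider interval also makes non-inferiority harder to claim. Both statements are correct, so a reading of systematic bias would be unsupported. However, the article states no margins for the secondary outcomes, and where the aim is to look for harm a wider interval is still less informative.

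**Conclusion.** The point holds as a modest one about efficiency. The printed covariate list omits the outcome's own baseline where Table 2 shows it will be available, and it differs in this from the primary analysis. Applied as printed, it would forgo a reduction in standard error of about 2% to 25% for continuous secondary and caregiver outcomes, beyond adjustment for symptom severity. That range rests wholly on assumed correlations. At the low end the loss is trivial; at the high end the interval half-width would be 0.27 rather than 0.20 SD. Body mass index may lie toward the high end if it is stable over a year, but the documents do not show this. No size is claimed for binary or event outcomes. Whether any loss will occur depends on Additional file 3 and the statistical analysis plan.

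**What to change.** In Analysis of secondary outcomes, extend the covariate list with: *and the baseline value of the same measure where collected*. The words *where collected* exclude quality of care and adverse events. Then check that Additional file 3 and the statistical analysis plan say the same. If they already include the term, only the article's wording needs to be brought into line. For binary and event-type outcomes, those documents should say how baseline status enters the model.

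The cost is one clause and a consistency check. The measurements are already scheduled, so no new data are needed. The change should be made before unmasked outcome data are seen.

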#### Economic analysis

The economic analysis will measure both the costs associated with a task-sharing model of care, as well as the consequential impact on service use. Local unit costs will be applied to resources used so as to estimate changes in services costs in both intervention and comparator groups. Time lost from work by people with SMD and their caregivers will be valued using appropriate wage rates, adjusted to take account of patterns of employment in an agrarian economy. Costs will be analysed using multiple regression analysis so that the effect of the intervention on costs can be estimated whilst adjusting for differences in participant characteristics. Non-parametric bootstrap methods will be used if the residuals of the regression model are non-normally distributed. Further regression models will include the main clinical measures so that the relationship between costs and outcomes can be assessed. A cost-effectiveness analysis will be carried out. Differences in cost and primary outcome measure (BPRS-E) that take into account the uncertainty around point estimates will be plotted and subsequently presented as a cost-effectiveness acceptability curve.

### Ethical considerations

Ethical approval for the trial has been obtained from the Institutional Review Board of the College of Health Sciences, Addis Ababa University (Reference Number 030/12/Psy), the AHRI-ALERT Ethics Review Committee (Reference Number P037/13), the National Research Ethics Review Committee of Ethiopia (Reference Number 3.10/758/07), the Food, Medicine and Health Care Administration and Control Authority (Reference Number 02/6/22/13), the University of Cape Town Human Research Ethics Committee (Reference Number 226/2011) and the National Institute of Mental Health Data Safety and Monitoring Board (DSMB).

The trial will include people with SMD who lack capacity to consent to participate in the trial as long as they are not actively refusing and they have a guardian who gives permission. Given the lack of knowledge on task-sharing care for people with SMD, and the intention of the Ethiopian Ministry of Health to implement this new model of service provision, it is crucial that people with SMD who are representative of those who will receive the task sharing model in the future have the opportunity to participate in the study. In participants who lack capacity at baseline, the capacity to consent will be reviewed at follow-up assessment time-points. If the participant regains capacity, they will be informed about the trial and will only continue in the trial if they give informed consent. No out-patient treatment from non-specialist mental health workers will be provided to people with any mental disorder against their will, except for management of acute behavioural disturbance where the person poses an imminent risk to themselves or others.

There is genuine uncertainty as to whether or not a task-sharing model of mental health care for SMD can be as effective as mental health care delivered by mental health specialists, but also no evidence that it is any worse, supporting a position of clinical equipoise. In the absence of any difference in effectiveness of care, a task-sharing model of care may be preferred through being locally available, even if the practitioners delivering the care are not specialists.

During the trial period participants will directly benefit from free treatment for both mental and physical health problems. Participants will be compensated for transport and their time when attending for trial-related assessments. Transport costs for attending Butajira hospital will also be covered.

We anticipate that the main risks for those allocated to the task-sharing model of mental health care in PHC will be modest: 1) moving from a familiar arrangement to a new treatment setting may be unsettling at the beginning, and therefore, monthly reviews will be scheduled at the beginning of the trial in order to facilitate engagement; and 2) there is a risk of receiving inferior care, which will be detected through monitoring of clinical records, supervision and the 12 month interim analysis. It is not anticipated that either arm of the trial will be associated with an increase in serious or other adverse events; however, procedures are in place for minimising the risk of adverse events and ensuring monitoring, reporting and management of adverse events to the DSMB and other regulatory bodies. The risk of suicide will be minimised by excluding people who express active suicidal intent at the time of recruitment and requiring clinicians to use structured clinical follow-up forms that prompt for screening for suicide risk. The phased nature of recruitment is also designed to reduce risk of adverse events by ensuring that PHC workers have gained competence in managing care of people with stable or uncomplicated SMD before they take on the care of people with more complex illness. The occurrence of serious or other adverse events will be formally reviewed at 12 months as part of the interim analysis.

All trial-related assessments will take place in a location that respects the participant’s privacy. The confidentiality of the participants will be respected, and the names of the patients will not be quoted or published.

The trial will be subjected to rigorous on-site monitoring of safety and quality at study initiation and thereafter twice per year by an independent external monitor reporting to the NIMH DSMB, in addition to routine reporting to the NIMH DSMB twice per year.

## Discussion

A pressing need exists to scale up evidence-based packages of mental health care in LMICs and thereby improve the clinical, functional and social outcomes of people with mental disorders. Alongside this imperative runs a critical need to evaluate the success of the task-sharing models of mental health care, which are proposed as solutions to the treatment gap for mental disorders. Human resource and health system constraints mean that interventions that are demonstrated to be efficacious when evaluated individually cannot be assumed to be effective when delivered as part of a service in more real-world conditions. The dearth of high-quality mental health service trials from LMICs generally, and from low-income countries in particular, is a serious impediment to the successful scale-up of mental health care. The TaSCS trial seeks to provide high-quality evidence that will be timely for informing mental health care scale-up in other rural, low-income countries, as well as contributing to the international discourse on task sharing as an acceptable model of care for people with SMD.

### Trial status

Recruitment started on 13 March 2015 and is ongoing.

## Abbreviations

mhGAP: mental health Gap Action Programme
MHSSS: Mental Health Service Satisfaction Scale
PHC: primary healthcare
SMD: severe mental disorder
WHO: World Health Organisation
